## Design

LABOR is a randomized, controlled, non-inferiority trial. Patients will be randomly allocated to receive a mesh repair of their incisional hernia with either laparoscopic bridging or open anatomical reconstruction. The trial has been registered on Current Controlled Trials as ISRCTN93729016.

### Sample size calculation, randomization and statistical analysis

On the basis of a previous published work, the minimum DLL to define the non-inferiority of laparoscopic bridging vs. anatomic open reconstruction will be set to 5 degrees with a standard deviation of 8.5 degrees. With this hypothesis and for a power of 90% and an alpha of 5%, we will need 50 patients in each arm (total 100). If we consider a possible dropout rate of 10%, a total of 110 patients would be sufficient. As a consequence, approximately 20 patients for each center will be required.

A centralized block randomization stratified for center will be performed by a statistician not involved in patient management. Blocks will have a variable dimension (random) between 4 and 12 units. A total of five blocks will be obtained for each center in the event that the investigator continues enrollment beyond the initially planned sample size. The local investigators, after obtaining written informed consent of patients, will receive the randomization arm from the statistical center for each patient, then the patient will be allocated to the treatment group as indicated.

Data analysis will be performed by a statistician not involved in data collection at the main investigation center (University of Genoa). The means and standard deviations or medians with ranges, if asymmetry of data is detected, will be reported for all continuous demographic and clinical characteristics recorded, whereas counts and percentages will be recorded for categorical characteristics (e.g., gender, functional status and smoking habits).

To compare the DLL test results during follow-up between the two groups of treatment, ANOVA for repeated measures will be adopted using DLL as the dependent variable. Because the DLL test cannot have a normal distribution, a ranking transformation will eventually be used. The same approach will be used for the other ordinal characteristics used as secondary outcomes (VAS as scoring for pain and AWS score) and, in general, for all other outcomes considered. If a consistent number of missing values is detected during the follow-up, ANOVA for repeated measures will be replaced by linear mixed or generalized estimating equation (GEE) models, which permit the exclusion of the data only from a single missing observation and not from the patient on overall as with ANOVA. Single comparisons between baseline values and each time during follow-up will be assessed using Bonferroni correction for multiple comparisons. All analyses will be performed on an intention-to-treat basis. A *p*-value lower than 0.05 will be considered statistically significant. SPSS (v.20, IBM Corp., Armonk, NY, USA) will be used for the statistical analyses.

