### Participants

The researchers will recruit consecutive patients who are affected by an incisional hernia scheduled for surgical repair and meet the criteria for enrollment over a period of approximately 1 year. The patients in the participating units will be screened daily. Demographic data on screened patients, regardless of meeting enrollment criteria, will be recorded (registry: age, gender and type of surgery). We will randomize 110 patients admitted into the participating centers. It is expected that each participating center will randomize at least 20 patients who will meet all of the inclusion criteria.

Based on the current literature [19], it was decided to enroll patients with a defect suitable for both laparoscopic and open repair. For this reason, we have set the upper limit of the defect size at a width of 10 cm. We decided to set 60 years old as the cutoff age because that is the mean age in recent high-quality, randomized studies [4], and this cutoff value will minimize the difference in trunk flexor strength observed in previously cited papers and generated by differences in age [17].

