### Setting

Patients will be enrolled at six different surgical units across Italy, tertiary referral centers for both laparoscopy and abdominal wall surgery (three university teaching hospitals). The involved surgeons are experienced in the field of abdominal wall reconstruction and advanced laparoscopic techniques and have treated at least 20 cases for each trial procedure [21].

At least two investigators from each participating center will be involved in the study. One researcher will receive the allocation treatment for the patient after calling the statistician of the main investigation center (University of Genoa). The other investigator, blinded to the randomization arm, will score the primary and secondary postoperative endpoints.

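### Fifty per arm gives 90% power only for a one-sided 5% non-inferiority test, but the planned ANOVA at p<0.05 is non-directional, and at that level power is about 83–84%

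*Protocol article*

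**What the plan says.** The Design section states: "LABOR is a randomized, controlled, non-inferiority trial". In the section on sample size calculation, randomization and statistical analysis, the non-inferiority limit on DLL "will be set to 5 degrees with a standard deviation of 8.5 degrees", and the result is: "With this hypothesis and for a power of 90% and an alpha of 5%, we will need 50 patients in each arm (total 100". No sidedness is attached to that alpha.

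The same section then plans a repeated-measures ANOVA with DLL as the dependent variable, possibly after a rank transformation. Mixed or GEE models replace it if many values are missing. The decision rule is a p-value "lower than 0.05 will be considered statistically significant". It gives no sidedness and no confidence level, and it has no step that sets the estimated difference against 5 degrees.

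On numbers to recruit, the section adds: "If we consider a possible dropout rate of 10%, a total of 110 patients would be sufficient". The Setting section says "Patients will be enrolled at six different surgical units across Italy", and the Participants section says "It is expected that each participating center will randomize at least 20 patients", with 110 to be randomized overall.

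**The concern.** A non-inferiority sample size has a meaning only together with the level of the test that will be used. Here the calculation appears to rest on one level and the analysis on another, and the article does not say which governs the non-inferiority conclusion.

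Two things are at stake:

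- **Power.** If the 5% in the analysis is the usual non-directional 5%, the trial has less than its stated 90% power.
- **Error rate.** The risk of wrongly declaring laparoscopic bridging non-inferior is 5% on one reading and 2.5% on the other. A level that is not fixed in advance could be chosen once the data are known.

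The Clinical implications section would use the result to call bridging a valid alternative to open repair in patients over 60, so the level matters for the trial's main message.

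**Working it through.** **Inputs**

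- Margin 5 degrees, SD 8.5 degrees, power 90%, alpha 5%, equal arms of 50: sample size section.
- Non-inferiority design: Design section.
- True difference 0: my assumption. The article gives no value, though its hypothesis is that the two techniques are similar.

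**Formula**

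n per arm = 2 × (z_alpha + z_beta)² × SD² / margin², where 2 × 8.5² / 5² = 2 × 72.25 / 25 = 5.78 and z_beta = 1.2816 for 90% power.

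**Step 1: the plan's own figure**

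At one-sided 5%, z_alpha = 1.645. Then n = 5.78 × (1.645 + 1.2816)² = 49.5, rounded up to 50 per arm. This matches the article.

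**Step 2: the non-directional 5% level**

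A two-group ANOVA F test at p<0.05 counts differences in both directions. For a non-inferiority bound, the matching level is one-sided 2.5%, with z_alpha = 1.960. Then n = 5.78 × (1.960 + 1.2816)² = 60.7, rounded up to 61 per arm (62 by the t distribution). This does not match the article.

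**Step 3: power with the planned 50 per arm**

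The standard error of the difference is 8.5 × √(2/50) = 1.70, and 5 / 1.70 = 2.941. Power is Φ(2.941 − z_alpha).

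| Level | Power, normal | Power, t |
|---|---|---|
| One-sided 5% | 90.3% | 89.9% |
| One-sided 2.5% (non-directional 5%) | 83.7% | 83.0% |

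The second row is also, to rounding, the power of a non-directional 5% test to detect a true difference of 5 degrees. So the figure applies whether the 12-month comparison is read as a margin test or as a test for a difference.

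**Step 4: dropout**

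110 × 0.9 = 99 completers, or 49.5 per arm. The normal approximation gives 90.0% power at one-sided 5% and 83.3% at one-sided 2.5%. Dividing instead of multiplying gives 50 / 0.9 = 55.6, so 56 per arm and 112 in total, two more than planned.

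**Step 5: centres**

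6 × 20 = 120, against 110 to be randomized; 110 / 6 = 18.3 per centre.

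**The case against.** The strongest reply is that nothing is miscalculated. Non-inferiority is a one-sided question, a one-sided 5% level gives exactly 50 per arm, and so the calculation itself reveals the level intended. On this view, one-sided 2.5% is a convention brought in from outside, and a condensed article may leave sidedness and confidence level to the full protocol or analysis plan.

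Much of this stands. A reader might infer that the article commits itself to a two-sided test or a 95% confidence interval and then breaks that commitment. It does not: neither term appears. Nor can the 50 per arm be called an arithmetic error.

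The reply does not remove the mismatch. The article chose to state alpha, power, sample size, test and significance threshold together, and they do not fit. The test it names is non-directional and never uses the margin that produced the sample size. This is more than a detail left out.

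It is also fair to object that 83–84% is not the power of the repeated-measures ANOVA itself. That depends on the pattern over visits and on correlations the article does not give. The figure is for a single 12-month comparison, the time point of the primary outcome. Adjusting for baseline might recover some power, but the amount cannot be worked out, because the article does not say whether 8.5 degrees is the SD of the 12-month angle or of the change from baseline.

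A reader might further infer that 110 patients fail to cover 10% dropout. Under the level that the calculation implies, 99 completers still give 90.0% power, so this is rounding. The centre figures are loose wording: the sample size section itself says approximately 20 per centre, and no power or error rate depends on them.

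**Conclusion.** The point holds as a mismatch between the stated sample size and the stated analysis, not as a miscalculated sample size. The figure of 50 per arm belongs to a one-sided 5% margin test that the article neither names nor plans. At the non-directional 5% level of the test it does plan, a 12-month comparison with 50 per arm has about 83–84% power. The type II risk is then about 16–17% instead of 10%, and 90% power would need 61–62 per arm.

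These figures assume a true difference of 0 for the margin test, an SD of 8.5 degrees that applies to the quantity compared at 12 months, and no baseline adjustment. The dropout and centre figures are minor remarks on wording.

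**What to change.** In the sample size section, state the level and sidedness, and use the same level in the analysis paragraph with an explicit comparison against the margin, in degrees. Either of these is coherent:

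- Non-inferiority on 12-month DLL is tested at one-sided 5%, by comparing the relevant bound of the 90% confidence interval for the difference with 5 degrees. Power stays at about 90%.
- Non-inferiority is judged from a two-sided 95% confidence interval against 5 degrees. Power is restated as about 83–84% for an unadjusted comparison.

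Fix the choice before any comparative data are seen. Both are changes of text and need no additional patients. Keeping 90% power under the second option would take 122–124 evaluable patients, or 136–138 randomized after division by 0.9.

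As tidying only, either give the expected number of completers as 99 or raise the total to 112 (two more patients), and make the per-centre expectation agree with six centres and the total.

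### Randomisation is stratified by centre but the described DLL analysis has no centre term: if DLL differs between centres, standard errors are slightly too large, which one model factor would cure

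*Protocol article*

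**What the plan says.** All from the protocol article.

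- **Allocation** (Sample size calculation, randomization and statistical analysis): "A centralized block randomization stratified for center will be performed by a statistician not involved in patient management". No other stratification factor is named. On block size: "Blocks will have a variable dimension (random) between 4 and 12 units".
- **Centres** (Setting): "Patients will be enrolled at six different surgical units across Italy". The planned total is 110 patients.
- **Analysis** (same section as allocation): "To compare the DLL test results during follow-up between the two groups of treatment, ANOVA for repeated measures will be adopted", with DLL as dependent variable. If many values are missing, "ANOVA for repeated measures will be replaced by linear mixed or generalized estimating equation (GEE) models". The same approach is extended to the other outcomes.

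The section also covers a rank transformation, a Bonferroni correction, the analysis set, the significance level and the software. It names no centre term, and no text says that centre is excluded.

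**The concern.** Stratified blocks balance the arms within each centre, so differences between centres largely drop out of the treatment contrast. An analysis without centre still leaves those differences in its error term. The reported standard error then describes a less precise trial than the one that was run.

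Differences between centres are plausible here. Each unit has its own surgeons and its own blinded assessor, the DLL endpoint depends on a judgement of when the pelvis tilts, and a common mesh is only encouraged. At stake is some of the precision that the stratification was meant to provide.

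**Working it through.** **Inputs from the article.** Margin 5 degrees, SD 8.5 degrees, power 90%, alpha 5%, 50 per arm, 110 with dropout, six units, random blocks of 4 to 12.

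**Assumption.** The share of DLL variance that lies between centres (ICC) is not given. It is ranged below.

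**1. The plan's own figure.** n per arm = 2 × (8.5/5)² × (1.645 + 1.282)² = 49.5, so 50. The stated size is reproduced with alpha 5% one-sided; one-sided 2.5% would give 61. The planned standard error is 8.5 × √(2/50) = 1.70.

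**2. Effect of omitting centre, closed form.** With allocation balanced within centre, the true standard error of the difference is about 1.70 × √(1 − ICC), whether or not centre is in the model. Without centre, the model still reports about 1.70.

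- Power without centre = Φ[(5 − 1.645 × 1.70) / (1.70 × √(1 − ICC))]
- Power with centre = Φ[5 / (1.70 × √(1 − ICC)) − 1.645]

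| ICC | Without centre | With centre | Gain (points) |
|---|---|---|---|
| 0 | 90.3% | 90.3% | 0 |
| 0.05 | 90.8% | 91.5% | 0.7 |
| 0.10 | 91.4% | 92.7% | 1.3 |
| 0.15 | 92.0% | 93.9% | 1.9 |

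**3. Simulation.** Six centres, 100 patients analysed, even block sizes 4 to 12 equally likely, normal outcome, total SD 8.5, two-group comparison at 12 months, 4,000 runs per ICC. Centre is fitted as a fixed effect or left out.

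| ICC | Model SE / true SE, no centre | One-sided type I error, no centre | Power without / with centre |
|---|---|---|---|
| 0 | 0.99 | 5.5% | 89.1 / 89.0% |
| 0.05 | 1.02 | 4.4% | 90.2 / 90.8% |
| 0.10 | 1.04 | 4.2% | 91.7 / 92.9% |
| 0.20 | 1.10 | 3.6% | 92.8 / 94.9% |

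With centre in the model, type I error stays near 5% throughout (4.6% to 5.5%). Simulation error on a 5% rate is √(0.05 × 0.95/4000) = 0.34 points, so the departures from 5% at ICC 0 are noise. At ICC 0 adding centre costs essentially no power.

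**4. Imbalance within centres.** 110/6 = 18.3 patients per centre. Simulating centres of 18 or 19, the mean absolute difference between arms within a centre is 0.9 patients and the 95th percentile is 2. A difference of 4 or more occurs in about 1.2% of centres, and the largest seen is 6. The spread of the treatment estimate is almost the same without and with centre: 1.617 against 1.616 at ICC 0.10.

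**The case against.** **The article is silent; it does not exclude centre.** This is the strongest objection. A covariate list is commonly left to the statistical analysis plan, which is not shown. A reader might infer that the sponsor decided against adjusting for centre, and the text does not support that. What remains is that the section describes the analysis down to the rank transformation, multiplicity correction and software. Followed as written, it ignores the only stratification factor.

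**The effect is conditional.** It vanishes at ICC 0. The primary outcome is change from baseline, and stable differences between centres or examiners cancel in a change score. Reading the DLL angle by software from a photograph should also reduce examiner variation. Both points stand and argue for the lower end of the range. Differences between centres in the change itself would remain.

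**The error is conservative.** Against the 5-degree margin an oversized standard error cannot manufacture non-inferiority, and that stands. The reassurance is incomplete, because the abstract's Discussion and the Clinical implications section take a finding of no difference as acceptance of the null. Read that way, an inflated standard error makes the hypothesised conclusion easier to reach.

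**Two stronger readings fail.**
- A reader might compare 90% power without centre with 91.5% to 93.9% with it at ICC 0.05 to 0.15, or convert this to 53 to 59 patients per arm instead of 50. The 90% baseline is wrong, because stratified allocation has already lowered the sampling variance of the unadjusted difference. The gain is 0.7 to 1.9 points.
- A reader might infer from blocks of up to 12 that centres will end well out of balance and distort the treatment contrast. A difference of 6 in a centre is possible, but the usual difference is 0 to 2.

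**Conclusion.** The point holds as a modest mismatch between the randomisation and the described analysis. If DLL or its change varies between centres, the model standard error is too large by about 2% to 4% at an assumed ICC of 0.05 to 0.10 and about 10% at 0.20. One-sided type I error falls to about 4.4% to 3.6%, and about 0.6 to 2 points of power are given away.

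These sizes rest on an ICC that the article does not supply, on roughly equal centre sizes and on a normal outcome compared at 12 months. They do not cover a rank-transformed analysis. The stated sample size is unaffected, bias from imbalance within centres is negligible, and nothing here threatens a non-inferiority claim tested against the margin. It is a free improvement, held with moderate confidence because it rests partly on what the article does not say.

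**What to change.** State that centre (six levels) enters as a factor in the primary DLL model, in the linear mixed or GEE model that may replace it, and in the models for the secondary outcomes. If the statistical analysis plan already says so, one confirming sentence is enough.

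The cost is 5 degrees of freedom out of about 100 analysed patients. Centre is already known from randomisation, so sample size, visits and data collection do not change.

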**Methods and design:**

The LABOR trial is a multicenter, prospective, two-arm, single-blinded, randomized trial. Patients of more than 60 years of age with a defect of less than 10 cm at its greatest diameter will be randomly submitted to open Rives or laparoscopic defect repair. All the participating patients will have a preoperative evaluation of their abdominal wall strength and mobility along with volumetry, respiratory function test, intraabdominal pressure and quality of life assessment.

The primary outcome will be the difference in abdominal wall strength as measured by a double leg-lowering test performed at 12 months postoperatively. The secondary outcomes will be the rate of recurrence and changes in baseline abdominal mobility, respiratory function tests, intraabdominal pressure, CT volumetry and quality of life at 6 and 12 months postoperatively.

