Surprisingly and in opposition to previous studies included in the Cochrane review, a recently published randomized trial [16] indicated that postoperative pain and recovery at 3 weeks is not affected by the type of adopted hernia repair, but the laparoscopic approach results in better physical function than the open repair based on SF36 subscale values. This observation is only partly the consequence of the reduced number of surgical site infections following laparoscopy. Moreover, these findings could support the hypothesis that procedures aimed at restoring the anatomy that involve extensive and potentially damaging dissection in an already scarred myoaponeurotic region could be less effective for the patient. In other words, in certain circumstances, anatomic reconstruction could be an excessive burden for an already compromised abdominal wall. Nevertheless, a self-reported questionnaire cannot be accepted as the sole explanation of this phenomenon, which should be objectively investigated and measured.

To obtain an answer to the debate, an emerging type of analysis is being more frequently used: the functional evaluation of the motility and muscular strength of the abdominal wall. The modalities to evaluate the trunk flexor muscles and the strength of the abdominal wall are isokinetic dynamometer measurement and physical testing.

The isokinetic dynamometer (Biodex Model 2000, Multijoint System 3, Biodex Corp., Shirley, NY, USA) is a safe way to load a dynamically contracting muscle to maximum capability throughout its entire range in a continuous motion and to evaluate the trunk flexor strength during isokinetic movement at a constant angular velocity. An inexpensive alternative to using a machine for evaluation is the use of physical tests. The most commonly used tests are the double leg-lowering test (DLL) and the trunk-raising test (TR). Both of them explore the strength of the rectal muscle, asking the patient to perform some curl-type exercises. After categorization of DLL and TR, it is possible to create an abdominal wall strength score (AWS) with a minimum score of 0 and a maximum of 10 points.

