Thus far, the aforementioned instruments have been used in two published studies without resolving the debate over the best intervention between bridging and reconstruction of the abdominal wall. The dynamometer was used in a study by den Hartog and coworkers [17] in which trunk flexor strength was compared for a group of 30 patients submitted to laparoscopic or open hernia repair with rectal approximation and a group of 12 healthy subjects. The mean torque/weight (N m/kg) for trunk flexion was significantly higher in the control group compared with that of the incisional hernia repair patients. Moreover, among the patients who underwent surgery, a significantly higher peak torque/weight was observed in the open technique group compared with the laparoscopic technique group. Based on these measures, the authors considered the two-layered technique more effective in repairing the abdominal wall of patients with incisional hernias and even more protective against some types of complication (back pain) in comparison with laparoscopic bridging. The multiple limitations represented by the fact that the study was not prospective and largely underpowered and that the patients in the open surgical group were submitted to a repair without mesh make the results not completely reliable.

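### The primary outcome is DLL at 12 months, but the only between-arm analysis named is a repeated-measures ANOVA, neither of whose between-arm terms estimates the 12-month difference

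*Protocol article*

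**What the plan says.** - **Design.** "LABOR is a randomized, controlled, non-inferiority trial" (Protocol article, Design).
- **Primary outcome.** The abstract gives it as the "difference in abdominal wall strength as measured by a double leg-lowering test performed at 12 months postoperatively". The Aim of the study also places it at 1 year. The Primary outcome section defines it as change from baseline at 12 months. The Secondary outcome section lists DLL before surgery and at 1 and 6 months as secondary.
- **Sample size.** The non-inferiority limit "will be set to 5 degrees with a standard deviation of 8.5 degrees". With 90% power and 5% alpha this gives 50 patients per arm (Sample size calculation, randomization and statistical analysis).
- **Between-arm analysis.** The same section states: "To compare the DLL test results during follow-up between the two groups of treatment, ANOVA for repeated measures will be adopted using DLL". A linear mixed or GEE model replaces it if many values are missing. All other outcomes follow the same approach.
- **Visit-specific comparisons.** The only ones named set baseline against each later time, with Bonferroni correction.

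The section does not say which ANOVA term decides, or whether baseline is one of the levels. It names no comparison of the arms at 12 months.

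**The concern.** The endpoint and the sample size concern one number, the difference between arms at month 12. The named analysis has two terms that involve the arms, and neither is that number.

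The group effect is the equally weighted mean of the visit differences, so outcomes the protocol calls secondary weigh as much as the primary visit. If baseline is a level, it adds a visit at which randomization makes the expected difference zero. In a non-inferiority trial, a loss that builds up by 12 months can then look smaller than it is, and bridging can pass when it should fail.

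The group-by-time effect asks whether the difference varies over visits. It can be significant because of an early recovery difference that has gone by month 12. On follow-up visits alone, it cannot see a loss that is the same at every visit.

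The two terms can therefore lead to opposite conclusions from the same data, and the text does not settle which one counts.

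**Working it through.** **Inputs from the protocol.** Margin 5 degrees, SD 8.5 degrees, alpha 5%, power 90%, 50 per arm; DLL measured before surgery and at 1, 6 and 12 months.

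**Assumptions, not in the protocol.** The SD of 8.5 applies at each visit. All pairs of visits have the same correlation ρ, taken over 0.3 to 0.9. The margin is applied to the group effect at one-sided 5%. The loss patterns are illustrative. "Loss" means open minus bridging, in degrees.

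**1. The plan's own figure.** n per arm = 2 × (1.645 + 1.282)² × 8.5² / 5² = 49.5, so 50. This matches. It is a single-time-point, one-sided 5% calculation. One-sided 2.5% would need 61.

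**2. What a month-12 contrast would do.** SE = 8.5 × √(2/50) = 1.70. Power at no true difference = Φ(5/1.70 − 1.645) = 90%. A true loss of exactly 5 degrees passes 5% of the time.

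**3. What the group effect does.** With k visits, SE = 8.5 × √[(1 + (k − 1)ρ)/k] × √(2/50), and P(pass) = Φ((5 − mean loss)/SE − 1.645).

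Worked case: loss 0/2.5/5 at 1/6/12 months, follow-up visits only (k = 3), ρ = 0.3. The mean loss is 7.5/3 = 2.5 and SE = 1.70 × √(1.6/3) = 1.24. P(pass) = Φ(2.5/1.24 − 1.645) = 64%. At ρ = 0.9, SE = 1.64 and P(pass) = 45%.

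In every row below the true 12-month loss is 5 degrees, so the pass rate should be 5%. Ranges cover ρ from 0.3 to 0.9.

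| Loss at 1/6/12 months | Follow-up only: mean, P(pass) | Baseline also a level: mean, P(pass) |
|---|---|---|
| 0/0/5 | 1.67, 65–85% | 1.25, 74–94% |
| 0/2.5/5 | 2.50, 45–64% | 1.88, 61–85% |
| 5/5/5 | 5.00, 5% | 3.75, 19–28% |
| 10/7.5/5 | 7.50, about 0% | 5.62, about 2% |

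**4. What the group-by-time effect does.** Noncentral F with noncentrality (50/2) × Σ(d − mean d)² / [8.5² × (1 − ρ)], where d is the difference at each visit.

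- *Early difference that disappears, 0/5/2/0 from baseline to 12 months.* Σ = 16.75. At ρ = 0.6 the noncentrality is 25 × 16.75 / 28.9 = 14.5, and F(3, 294) is significant 90% of the time. Over ρ = 0.5–0.7 the range is 82–97%, although the 12-month difference is zero. On follow-up visits only it is 75–93%.
- *Late loss, 0/0/2.5/5 from baseline.* Σ = 17.19. It is significant 91% of the time at ρ = 0.6, and 83% at ρ = 0.5. This term would usually flag such a loss.
- *Constant loss of 5 on follow-up visits only.* Σ = 0, so it is significant only at the 5% error rate and misses the loss about 95% of the time.

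**The case against.** The strongest reply is that the harm depends on a choice the text does not make. A reader might infer that a 12-month loss will be averaged away by baseline and early visits. The protocol does not support that as a certainty: it does not say that the group effect is the deciding term, and its reference to results during follow-up may exclude baseline. If the deciding term is group-by-time with baseline as a level, a late loss would usually be detected. Averaging is also not always lenient: a constant loss over follow-up visits is not diluted, and a larger early loss works against bridging. All of this stands, and it limits the claim.

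A reader might also infer from the Background that the arms will differ in opposite directions early and late. The support is weak. The trial in which "the laparoscopic approach results in better physical function than the open repair based on SF36 subscale values" found no difference in pain and recovery at 3 weeks, and the Background elsewhere mentions a possible short-term benefit of open closure. The dynamometer study in which "a significantly higher peak torque/weight was observed in the open technique group compared with the laparoscopic technique group" is described without a follow-up time, and the protocol itself regards it as not fully reliable. Neither measured DLL.

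The pass rates apply the margin to the group effect, whereas the analysis text gives only a p-value threshold, and the Discussion speaks of accepting the null hypothesis. That is a separate problem. The rates show what this estimator would do if tested against the stated margin.

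Finally, model details are often left to an analysis plan, and a month-12 contrast can be drawn from any of the named models. But the article does state the between-arm method and the visit-specific comparisons, and those stated do not address the endpoint. That is a mismatch between two stated things rather than condensed detail.

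**Conclusion.** The point holds in a conditional form. Endpoint, margin and sample size all refer to the 12-month difference, while the stated between-arm analysis has no term that estimates it. That follows from the text and needs no assumption.

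The size of the error depends on the deciding term, on whether baseline is a level, and on the course of the difference. For a loss building up to 5 degrees by month 12, the group effect would pass bridging 45–64% of the time on follow-up visits, or 61–85% with baseline included, against a nominal 5%. The group-by-time effect would usually catch that loss, but it can reject for a difference that no longer exists at 12 months. These figures rest on the assumed SD scale, equal correlation, loss patterns and use of the margin. They show what can happen and do not predict this trial's result. The correction matters because the non-inferiority conclusion rests on this comparison.

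**What to change.** State in the analysis section or the SAP that the primary analysis is the between-arm difference in DLL at the 12-month visit, adjusted for baseline DLL so that it matches the change-from-baseline definition in the Primary outcome section. Take it as the month-12 contrast from the repeated-measures or mixed model, with visit as a factor and a group-by-visit term, and compare its confidence limit with the 5-degree margin. Keep the group main effect and the omnibus group-by-time test as secondary. Use visit-specific contrasts in the same way for the other outcomes that follow this approach.

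The cost is a sentence or two. No new data, visits or patients are needed, and the sample size stays at 50 per arm, because the existing calculation is already for this comparison.
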